**Study Protocol**

**Protocol title:** A Phase 2, single-arm, phase 2 trial of rituximab plus lenalidomide in FL.

| Protocol number | NHL-R2 |
| --- | --- |
| Date: | 01 Sep, 2018 |
| Study Phase: | 2 |
| Study Design: | This is a phase 2 trial to evaluate the efficacy and safety of rituximab plus lenalidomide in patients with newly diagnosed FL. |
|  |  |

| **Synopsis** | |
| --- | --- |
| **Protocol Number:** NHL-R2 | **Study phase:** 2 |
| **Date of Protocol Synopsis:** 01 SEP, 2018 | |
| **Protocol Title:** A Phase 2, single-arm, phase 2 trial of rituximab plus lenalidomide in FL. | |
| **Objectives:**  **Primary objective:** The primary objective is to evaluate the complete response rate (CRR) at the end of treatment of rituximab plus lenalidomide in patients with newly diagnosed follicular lymphoma (FL).  **Secondary objectives:** The secondary objectives are to evaluate the complete response rate (ORR), progression free survival (PFS) and overall survival (OS). The safety will also be evaluated by number of participants with treatment-related adverse events as assessed by the Common Terminology Criteria for Adverse Events (CTCAE) version 4.0. | |
| **Study Sites:** Shanghai Rui Jin Hospital | |
| **Study Population:** Newly diagnosed patients with FL | |
| **Number of Subjects to be Enrolled:** 115 patients | |
| **Background:**  Non-Hodgkin lymphoma (NHL) is the indolent tumor originated in lymph nodes and other lymphoid tissues and the incidence is growing up at 3%-4% per year. Follicular lymphoma (FL) is a heterogeneous entity of non-Hodgkin lymphoma (NHL), accounting for 10%-20% of NHL. Rituximab, cyclophosphamide, doxorubicin, vincristine, and prednisolone (RCHOP) or RCHOP-like chemotherapy is widely used in FL. However, rituximab plus chemotherapy has considerable side effects, particularly hematological toxicity and non-hematological immunosuppression, gastrointestinal and cardiac events. Multiply combinational regimens have been attempted in FL, rituximab plus immunomodulatory agent lenalidomide (R2) achieve similar clinical efficacy as rituximab plus chemotherapy in newly diagnosed FL with less chemotherapy-associated side effects. We plan a phase 2, single-arm trial to evaluate the efficacy and safety of rituximab plus lenalidomide in a Chinese cohort of newly diagnosed patients with FL. | |
| **Diagnosis and Main Criteria for Inclusion/Exclusion:**  **Main Inclusion:**   - Newly diagnosed, histologically confirmed the following pathology subtype according to WHO 2008   classification: Follicular Lymphoma I-IIIA.   - ≥ 16 years of age. - Performance status of 2 or less. - Has no history of malignancy. - Has radiologically measurable disease. - Life expectancy ≥3months. - Voluntarily sign an informed consent. | |
| **Diagnosis and Main Criteria for Inclusion/Exclusion (Continued):**  **Main Exclusion:**   - Previous systemic chemotherapy or local therapy. - Has undergone hematopoietic stem-cell transplantation (HSCT). - Has previous treatment of lenalidomide. - Has an active infectious disease requiring general antibiotics, antifungal, or antiviral therapy. - Has an uncontrollable medical condition that might interfere with their participation in the study. - Echocardiography shows left ventricular ejection fraction (LVEF) ≤ 50%. - Woman in pregnancy or lactation. - Patient is known to be positive for Human immunodeficiency virus (HIV) infection. | |
| **Treatment** | |
| Study Group | Interventions |
| Rituximab plus lenalidomide Group | R2 (at each cycle):  Rituximab 375mg/m^2^, intravenously, Day 0  Lenalidomide 25mg, orally, Day 1-10  Every 21 days for 6 cycles |
| **Duration of Treatment:** A total of 6 cycles of treatment. | |
| **Criteria for Evaluation:**  **Efficacy:**  Positron emission tomography-computed tomography (PET-CT) will be evaluated at baseline, after three cycles for interim evaluation and at EOT for final evaluation. | |
| **Criteria for Evaluation (Continued):**  Responses will be assessed according to 2014 Lugano criteria for non-Hodgkin lymphoma. Central response assessment of PET and CT images will be performed by radiologists of Shanghai Ruijin Hospital, who are not informative of the treatment group. CT scans of the neck, thorax, abdomen, and pelvis will be repeated every three months thereafter to monitor disease progression in the first year, then every six months in the following two years, and yearly thereafter.  **Safety:**  The severity of adverse events will be assessed according to the CTCAE v4.0. | |
| **Statistical Plans:**  Statistical analysis will be conducted by or under the supervision of the study statistician. Statistical analysis will be performed using SPSS and GraphPad Prism.  The statistical analysis sets are defined as follows: The intention-to-treatment population (ITT) is defined as all subjects who were randomized to either of the treatment group and accepted at least one dose of treatment. ITT sets can be used for efficacy/safety analysis and demographic/baseline characteristics analysis.  The Fisher's exact test will be applied to categorical variables as appropriate. Analysis of covariance, or rank-sum test will be used, as appropriate, for continuous variables. Survival estimates will be calculated using Kaplan-Meier method. Log-rank test will be used to compare survival time between treatment groups. Univariate hazard estimates were generated with the Cox regression methods. Cox regression additionally required that the hazard ratio be proportional, which was calculated by Schoenfeld residual test. If the P value was ≥ 0.05, then the hazard ratio was considered proportional. Thereafter, variables with P value < 0.05 in univariate analyses were included in the multivariable sets.  The primary endpoint will be CRR at the end of treatment. Secondary endpoints will include ORR, PFS, OS and adverse events.  **Variable definition:**  Complete Response Rate (CRR): CRR was assessed by the investigators according to the Lugano 2014 criteria.  Objective response rate (ORR): ORR was defined as the proportion of patients with a complete response or partial response to treatment according to Lugano 2014 criteria.  Progression-Free Survival (PFS): PFS was defined as start date of treatment and ended with the date of disease progression or the last follow-up.  Overall Survival (OS): OS was recognized from start date of diagnosis and ended with the date of death or the last follow-up.  **Assumptions:**  We estimate that 73% of patients in the R2 group would achieve CR. One-hundred and fifty patients will be required to show this difference with 5% significance (two-sided) and 90% power. The number of patients achieving CR at the end of study will be reported by treatment group with 95% CI using normal approximation. Sample size was calculated by PASS software (NCSS, Kaysville, UT).  **Data quality assurance:**  To ensure good quality data, investigators and study site personnel will be familiarized with the study protocol, study procedures and principles of GCP during the trial initiation visit. All the data will be placed into the local database via a data registry server managed by the data collection group.  All adverse clinical experiences, whether observed by the investigator or reported by the patient, will be recorded, with details about the duration and intensity of each episode, the action taken with respect to the test drug, and the patient’s outcome. The investigator will evaluate each adverse experience for its relationship to the test drug and for its seriousness. CTCAE term (AE description) and grade: The descriptions and grading scales found in the revised NCI Common Terminology Criteria for the CTCAE v4.0. will be utilized for AE reporting. Concomitant medications will be coded using WHO Drug Reference List.  **Handling of missing data:**  Every effort will be made to contact patients who fail to return for scheduled visits. A patient is considered lost to follow-up if no information has been obtained by investigator for one year and at least three unsuccessful documented attempts of contact are available in source documentation. Missing or incomplete data for survival are managed by censored data analyses.  **Follow-up plan:**  Follow-up period will start at the end of treatment or at treatment discontinuation. Patient will be followed every 3 months for the first year and every 6 months up to end of follow-up period.  Follow-up assessments include:  • Physical examination including ECOG PS  • Hematology laboratory evaluations (RBC count, hemoglobin, hematocrit, WBC count and ANC, and platelet count)  • CT scans every 3 months for the first year and every 6 months for the second year and then every year until disease progression/relapse or end of follow-up period. | |

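### The central PET/CT readers are masked only to treatment group, which in a one-arm trial masks nothing, and the protocol names no other reader safeguard

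*Protocol*

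**What the plan says.** The title calls the study "A Phase 2, single-arm, phase 2 trial of rituximab plus lenalidomide in FL", and the Background repeats the design: "We plan a phase 2, single-arm trial to evaluate the efficacy and safety of rituximab plus lenalidomide". The Treatment table has one row, the "Rituximab plus lenalidomide Group", with R2 for 6 cycles. The site entry reads "Study Sites: Shanghai Rui Jin Hospital"; no other site is listed.

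Under Criteria for Evaluation, PET-CT is planned at baseline, after three cycles and at end of treatment, and "Responses will be assessed according to 2014 Lugano criteria for non-Hodgkin lymphoma". The continued part of that section assigns the central assessment to "radiologists of Shanghai Ruijin Hospital, who are not informative of the treatment group". It names nothing else that is withheld from the readers.

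Under Statistical Plans, "The primary endpoint will be CRR at the end of treatment". The variable definitions in the same section give the assessment of CRR to the investigators, by the same Lugano 2014 criteria, and do not mention the central read.

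**The concern.** Masking a reader to treatment group protects a comparison: it stops the reader from favouring one arm over another. With one arm there is no comparison to protect. What can sway a reader in such a trial is knowledge of how the patient is doing, above all the treating investigator's opinion of response and the later outcome. The protocol does not mention masking to either.

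Two things are at stake. First, a report that repeats the sentence would claim a masked read when the masking concealed nothing. Second, there is no concurrent control in which a lenient read would cancel out. If the central read feeds the primary endpoint, any net leniency enters the CRR directly.

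**Working it through.** The protocol gives no figure on this point, so there is none to reproduce. The check compares the protocol's own statements.

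**1. Does the stated masking conceal anything?**

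- Number of treatment groups: one (title, Background, Treatment table).
- Item concealed from the readers: treatment group (Criteria for Evaluation, continued).
- Anyone who knows that a scan belongs to this trial knows the group, because there is only one. The concealed item carries no information.

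**2. Is any other reader safeguard named?**

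- The response criteria are fixed (Lugano 2014). That limits discretion but is not masking.
- The central readers work at the hospital that is the only listed site, so the protocol describes no institutional separation from the treating team.
- Masking to time point, clinical data, the investigator's assessment or later outcome is not mentioned.

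**3. Does the central read reach the primary CRR?**

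| If CR is determined by | Consequence |
| --- | --- |
| the central radiologists (as Criteria for Evaluation suggests) | A lenient central read enters the CRR directly |
| the investigators (as the variable definitions state) | The central read is at most supportive, and leniency in it leaves the primary CRR unchanged |

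The protocol supports both rows and does not choose between them. The masking statement is empty in either case. In the second row the governing read is made by investigators who know the treatment.

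**4. Can the size be worked out?**

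If the central read governs, let u be the number of scans wrongly raised to CR, d the number wrongly lowered, and n the number of patients. Then

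observed CRR − true CRR = (u − d)/n.

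The documents give neither u nor d. Assumed values show only how the result follows the assumption. In the first three rows n = 115 (Number of Subjects to be Enrolled); the last uses the planned CR rate of 73% (Assumptions).

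| Assumption (none is in the documents) | Shift in CRR |
| --- | --- |
| u = d | 0 |
| 5% of scans borderline, half raised, d = 0: 0.05 × 115 = 5.75, half ≈ 3 | 3/115 = 2.6 points |
| 10% borderline, half raised, d = 0: 0.10 × 115 = 11.5, half ≈ 6 | 6/115 = 5.2 points |
| 5%, 10% or 20% of the 27% without CR read as CR, d = 0 | 0.05 × 27 = 1.35; 0.10 × 27 = 2.7; 0.20 × 27 = 5.4 points |

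For scale, the 95% half-width at 73% is 1.96 × √(0.73 × 0.27/115) = 8.1 points. With the 150 patients named under Assumptions it is 7.1 points. That interval covers sampling error only, not reader bias.

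**The case against.** Five objections deserve an answer.

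- **The primary endpoint may not depend on this read.** The variable definitions give CRR to the investigators. This stands. A reader might infer that an unmasked central read inflates the primary CRR, but the documents do not support that until the two places are reconciled.
- **The size is unsupported.** A reader might take 2.6 to 5.2 points as the likely bias. Both the borderline share and the half that is raised are assumed, and downgrades are set to zero. This stands; the figures are illustrations, not estimates.
- **Access to other information is not documented.** Working at the study hospital makes it possible for the readers to see local reports or the treating team's opinion, but the protocol does not say that they do. An imaging charter or statistical analysis plan that is not shown may restrict it. This stands against any claim that the readers are in fact unmasked to everything. It does not rescue the sentence, since no later document can give content to masking to treatment group in a one-arm trial.
- **The readers might not know that a scan is a trial scan.** The protocol does not say so, and it describes a dedicated central assessment at set time points. The objection carries little weight.
- **It is only leftover two-arm wording.** Statistical Plans has similar remnants: an analysis set defined by randomisation, a log-rank comparison of groups, and CR reported by group. A shared origin is plausible. Correcting those sentences would still leave the central read without a meaningful safeguard.

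**Conclusion.** The point holds in a limited form. The protocol states one reader safeguard, and the design empties it of content; this follows from the text and needs no assumption. If the central read determines or supports CR, the protocol as written gives it no stated protection against expectation bias. Here no stated protection means none in this protocol.

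The documents do not show that bias will occur, give no means of estimating it, and do not settle whether it could reach the primary CRR. The use of fixed Lugano 2014 criteria reduces the risk somewhat. The point justifies correcting the protocol because the correction is cheap, not because a known number of percentage points is at risk.

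**What to change.** 1. Delete the claim that the central readers are masked to treatment group.
2. State instead that the same central radiologists apply Lugano 2014 and record and lock their read without access to the investigator's response assessment or later outcome.
3. Reconcile Criteria for Evaluation with the variable definitions under Statistical Plans, so that one place says whose read determines CR for the primary endpoint.

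The cost is protocol wording, a read form with a lock step, and minor image handling. The readers and scans stay the same, and no extra readers are required. Withholding routine imaging reports or all clinical data is not needed: it could require separate readers at a single hospital and could hinder a Lugano assessment.

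### PFS is censored at the last follow-up rather than the last tumour assessment, so time in contact without CT counts as progression-free and PFS can be overstated

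*Protocol*

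**What the plan says.** All of this stands in the protocol synopsis.

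- **Statistical Plans, Variable definition.** "PFS was defined as start date of treatment and ended with the date of disease progression or the last follow-up". The OS definition that follows also closes on the last follow-up.
- **Role and estimator.** "Secondary endpoints will include ORR, PFS, OS and adverse events". "Survival estimates will be calculated using Kaplan-Meier method".
- **Criteria for Evaluation, Efficacy.** After the end-of-treatment PET-CT, repeat CT is the method named for monitoring progression: three-monthly in the first year, "then every six months in the following two years, and yearly thereafter".
- **Follow-up plan.** Visits: "Patient will be followed every 3 months for the first year and every 6 months up to end of follow-up period". They include physical examination and haematology. Imaging: "CT scans every 3 months for the first year and every 6 months for the second year and then every year".
- **Handling of missing data.** "A patient is considered lost to follow-up if no information has been obtained by investigator for one year" (with at least three documented failed contact attempts). Missing survival data are to be handled by censoring; missed scans are not mentioned.

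Nothing in the protocol moves PFS censoring to the last scan.

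**The concern.** One date closes two endpoints that need different information. Any contact shows that a patient is alive. It does not show that the disease has not progressed, particularly at a visit without imaging. Such visits are scheduled, because visits stay six-monthly after CT becomes yearly. A patient who has stopped CT can also stay in follow-up indefinitely, since loss to follow-up depends on having no information at all.

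That patient remains in the PFS risk set without an adequate search for the event. The Kaplan-Meier curve is then held up by person-time in which progression could easily go unrecorded. The trial has a single arm, so no concurrent control shares the distortion. What is at stake is the reported PFS, not the primary endpoint of CR rate at end of treatment.

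**Working it through.** **No PFS figure to reproduce.** The protocol gives no PFS rate, event count or missed-scan rate. The check therefore covers the direction of the effect and its size under stated assumptions.

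**Direction.** Each Kaplan-Meier factor is 1 − d/n (d events, n at risk). Both censoring dates keep the same recorded events, so d is unchanged. Last-follow-up censoring never makes n smaller. Its PFS estimate is therefore never below the one from last-CT censoring. Which of the two is nearer the truth depends on clinical detection, treated below.

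**Inputs from the protocol.** Six 21-day cycles (126 days) put end of treatment at about 4.1 months. CT follows the Follow-up plan: 3, 6, 9, 12, 18 and 24 months after end of treatment, then yearly. Visits are three-monthly in year 1, then six-monthly.

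**Assumptions not in the protocol.**
- Progression is exponential, with true 36-month PFS S36 of 80% or 70%.
- A share p stops CT, for reasons unrelated to disease, at a time uniform over the 24 months after end of treatment, and keeps attending visits.
- A share q of progressions is found clinically at visits.
- Every patient has at least 42 months of follow-up.

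PFS is read at month 41, just after the CT at 4.1 + 36 = 40.1 months.

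**Step 1: complete imaging.** F = S36^(40.1/36), which is 0.780 for 80% and 0.672 for 70%.

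**Step 2: patients who stop CT, with q = 0.** They appear progression-free at month 41 if they were so at their last CT. The last CT falls at 4.1, 7.1, 10.1 or 13.1 months (weight 3/24 each) or at 16.1 or 22.1 months (weight 6/24 each). With S(t) = S36^(t/36):
- 80%: M = 0.125 × (0.975 + 0.957 + 0.939 + 0.922) + 0.25 × (0.905 + 0.872) = 0.918
- 70%: M = 0.125 × (0.960 + 0.932 + 0.905 + 0.878) + 0.25 × (0.853 + 0.803) = 0.873

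**Step 3: overstatement under the written rule.** Approximately p × (1 − q) × (M − F), where M − F is 0.138 (80%) or 0.201 (70%).

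| True 36-month PFS | p | q = 0 | q = 50% | q = 100% |
|---|---|---|---|---|
| 80% | 10% | +1.4 | +0.7 | 0 |
| 80% | 20% | +2.8 | +1.4 | 0 |
| 70% | 10% | +2.0 | +1.0 | 0 |
| 70% | 20% | +4.0 | +2.0 | 0 |

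(percentage points; p = 0 gives 0 throughout)

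Simulation with n = 115 and q = 0 agrees: 79.4% and 80.9% (80% case) and 69.4% and 71.2% (70% case) for p = 10% and 20%.

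**Step 4: last-CT censoring, p = 20%, by simulation.** In the 80% case it returns 78.0% at q = 0, equal to complete imaging. At q = 50% it is about 1.3 to 1.5 points too low, and at q = 100% about 2.5 to 2.6 points too low. In the 70% case (complete imaging 67.1%) it gives 65.5% and 64.1%. The reason is that clinically found events are counted while clinically observed progression-free time is discarded.

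**Step 5: other horizons and the other CT schedule.** A separate simulation took q = 0, p = 10-30%, and CT stopping uniform on 6-30 months. The excess of last-follow-up over last-CT censoring in the 80% case was 0.7-2.0 points at 3 years on the Follow-up plan schedule, 1.0-2.9 on the Efficacy schedule, and 1.8-5.5 at 5 years. In the 70% case it was 1.0-4.4 points at 3 years and 2.5-7.9 at 5 years, across both schedules.

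**The case against.** The strongest reply is that follow-up visits include a physical examination and that nothing restricts a PFS event to progression seen on CT. A reader might infer that progression cannot be recorded without a scan, that the bias always runs upward, and that last-CT censoring recovers the fully imaged result. The protocol does not support this. Those statements need clinical detection to be at or near zero. With full clinical detection the written rule is unbiased and last-CT censoring is the rule that errs, downward. This objection stands and limits both the size and the remedy. It does not remove the point, because CT is the named method and nothing secures complete clinical detection.

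Three narrower replies also stand:
- A reader might infer that leaving treatment means leaving imaging. The Follow-up plan starts follow-up, including CT, at treatment discontinuation as well as at end of treatment. Only missed or declined CT matters.
- The gap between six-monthly visits and yearly CT does not inflate PFS by itself; with no missed scans the overstatement is nil. The loss-to-follow-up rule classifies patients and sets no censoring date. It shows only that contact without imaging keeps a patient in follow-up.
- The effect is modest against sampling error. With n = 115 and PFS of 80%, the 95% half-width is 1.96 × √(0.8 × 0.2 / 115) = 7.3 points. No hypothesis or sample size rests on PFS.

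It can also be said that an unseen analysis plan might define last follow-up as the last assessment. But the protocol fixes the date in words shared with OS, and the definition as written should be corrected.

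**Conclusion.** The point holds in a limited form. The protocol states a contact-based censoring date for an endpoint that depends on imaging, and PFS can be overstated as a result. The size is not knowable from the documents. It is about +1 to +4 points at month 41 if 10-20% of patients stop CT and no progression is found clinically, about half that if half of progressions are found at visits, and nil if nobody misses CT or all progressions are found clinically. Confidence is high about the wording and low about the size. Only a secondary endpoint is affected.

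Two linked defects bear on the remedy. The same sentence omits death as a PFS event, so a death without progression would be censored, which also raises PFS. Changing only the censoring date would leave that in place. And the Efficacy section has six-monthly CT in year 3 while the Follow-up plan has yearly CT from year 3. The gap between last scan and last follow-up depends on which applies, so these passages must be reconciled.

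**What to change.** Rewrite the PFS definition along these lines:

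- PFS runs from treatment start to first documented progression or death from any cause, whichever comes first.
- Patients without an event are censored at the last adequate tumour assessment (PET-CT or CT) showing no progression, or at treatment start if there is none after baseline.
- The last date known alive is the censoring date for OS only.
- State whether clinically detected progression counts as an event, and apply the same standard of evidence to events and to censoring dates.
- Report PFS censored at last follow-up as a sensitivity analysis. The spread between the two estimates shows how much missed imaging matters.

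Also reconcile the two CT schedules.

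The cost is a few sentences. The scans are already scheduled, so their dates should be available. PFS follow-up becomes slightly shorter and the estimate slightly less favourable. If many progressions are found only clinically, last-CT censoring brings some downward bias, which is why the evidence standard and the sensitivity analysis belong in the same edit.

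### PFS as defined leaves out death, so it is time to progression under another name and is overstated whenever a patient dies without progression

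*Protocol*

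**What the plan says.** All the relevant text is in the protocol synopsis, under Statistical Plans.

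- Variable definition, PFS: "PFS was defined as start date of treatment and ended with the date of disease progression or the last follow-up".
- Variable definition, OS, the next entry: "OS was recognized from start date of diagnosis and ended with the date of death or the last follow-up".
- Estimation: "Survival estimates will be calculated using Kaplan-Meier method".
- Role: "Secondary endpoints will include ORR, PFS, OS and adverse events".

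The PFS entry gives one disease event and one administrative ending. Nothing elsewhere in the protocol makes death a PFS event.

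**The concern.** PFS ordinarily treats death as a failure alongside progression. Here the only named failure is progression. The OS entry shows that the authors name death where they mean to count it, so the PFS entry cannot safely be read as including it silently.

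Deaths without documented progression are foreseeable in this population. The main eligibility criteria set no upper age limit, admit performance status up to 2 and ask for a life expectancy of only three months. A death between two scheduled scans may also leave no progression date.

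This is a single-arm trial, so PFS has no concurrent control and will naturally be read beside PFS from other studies. A version that drops deaths does not measure the same thing as one that counts them, and the difference favours the regimen. Any Cox model fitted to PFS would inherit the same event definition.

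**Working it through.** **No stated figure to reproduce.** The protocol gives no expected PFS rate, event count or power for PFS. Its only sample-size statement concerns complete response.

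**How the rule treats one patient.** Suppose a patient starts treatment, never has documented progression and dies.

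- Under the OS entry, the observation ends at death and is an event.
- Under the PFS entry, the progression ending does not apply. The only other ending is last follow-up, which Kaplan-Meier treats as censored.

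**Direction, without any model.** Take such a death with *n* patients at risk, and suppose the patient is censored at the date of death. The patient leaves the risk set at the same time under either coding. Coded as an event, the death multiplies the curve by (1 − 1/*n*); coded as censored, it multiplies it by 1. From that date on, the progression-only curve lies above the curve that counts the death. With no such deaths the two curves are identical.

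**Size, on assumed rates.** Let *p* be the 3-year risk of progression and *d* the 3-year risk of death without progression. Neither is in the protocol. With independent hazards:

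- progression-only estimate = 1 − *p*
- PFS counting deaths = (1 − *p*)(1 − *d*)
- overstatement = (1 − *p*) × *d*

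| *p* | *d* = 2% | *d* = 5% | *d* = 8% |
| --- | --- | --- | --- |
| 15% | 0.85 × 0.02 = 1.7 points | 0.85 × 0.05 = 4.25 | 0.85 × 0.08 = 6.8 |
| 20% | 0.80 × 0.02 = 1.6 | 0.80 × 0.05 = 4.0 | 0.80 × 0.08 = 6.4 |
| 30% | 0.70 × 0.02 = 1.4 | 0.70 × 0.05 = 3.5 | 0.70 × 0.08 = 5.6 |

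The middle case would be reported as 80.0%, against 0.80 × 0.95 = 76.0% with deaths counted.

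**Second parameterisation.** Assume constant hazards, a progression-only estimate of 80% at 3 years, and a yearly hazard λ of death without progression. PFS counting deaths is then 0.80 × exp(−3λ).

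| λ per year | PFS counting deaths | Overstatement |
| --- | --- | --- |
| 0.5% | 78.8% | 1.2 points |
| 1% | 77.6% | 2.4 |
| 2% | 75.3% | 4.7 |
| 3% | 73.1% | 6.9 |

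The two approaches agree at 3 years. Over horizons of 2 to 5 years, with progression-only estimates of 70% to 90% and the same λ range, the overstatement runs from 0.7 to 12.5 points.

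**The case against.** **The protocol never says that deaths are censored.** This is true. The PFS entry lists dates and does not code event against censoring. Censoring is an inference, but it is the only outcome open to a patient whose record ends without progression, and the contrast with the OS entry supports it.

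**An unseen SAP may count deaths.** It may. But the protocol does not leave the definition open; it states one. A SAP that added death would conflict with the protocol, and the sentence would still need correcting.

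**The effect may be small or nil, and PFS is secondary.** This stands. There is no hypothesis, threshold or power for PFS, every rate used above is assumed, and the low end is little more than one point.

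Four stronger readings are tempting, and the document does not carry them.

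- A reader might take the missing-data rule as an instruction to censor deaths: "Missing or incomplete data for survival are managed by censored data analyses". It follows the rule on loss to follow-up, and a recorded death is not missing data.
- A reader might infer informative censoring. The calculation above assumes independent hazards, so it shows only the gap between time to progression and PFS. Nothing in the protocol establishes dependence.
- A reader might infer that reported PFS could exceed OS. In the 80.0% versus 76.0% example, survival counted from the same start is 76% plus those who have progressed and are alive. It falls below 80% only if fewer than 4 of the roughly 20 points who progressed are alive, that is, if about 80% of them have died (1 − 4/20). Nothing in the protocol suggests this. It also starts OS at diagnosis and PFS at treatment, so the two are not on one clock.
- A reader might attach a fixed amount of unverified progression-free time to censoring at last follow-up. The protocol contradicts itself on when CT becomes yearly: after the third year under Criteria for Evaluation, after the second under Follow-up plan. Follow-up visits also include a physical examination. No single figure follows.

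**Conclusion.** The PFS definition is wrong as written. Its Kaplan-Meier estimate will be too high from the first death without documented progression. The direction follows from the definition and does not depend on the assumed rates; the size does. It is about 1.4 to 6.8 points at 3 years for assumed risks of 15% to 30% for progression and 2% to 8% for death without progression, under independent hazards, and zero if there are no such deaths.

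This should be fixed, but it does not threaten the trial's main conclusion. The primary complete response endpoint and its sample size do not depend on it.

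**What to change.** Replace the PFS sentence with a definition that runs from first dose to first documented progression or death from any cause, whichever comes first. State that patients alive without progression are censored, preferably at the last adequate tumour assessment.

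The censoring date is a secondary point and could be settled in the SAP. Before it is applied, the two CT schedules, under Criteria for Evaluation and under Follow-up plan, must be reconciled.

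The cost is one sentence in the protocol. Death dates are already required for OS, so no new data are collected and the sample size does not change. Reported PFS will be somewhat lower if any patient dies without progression. If the time-to-progression estimate is also wanted, it can be reported under that name.
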